### Ethical considerations

Full ethical approval has been obtained from the ethics committee of the Institute of Professional Psychology (IPP), Bahria University Karachi, Pakistan. The research team will fully comply with the International Conference on Harmonisation Good Clinical Practice (ICH-GCP) guidelines.

#### Data protection and confidentiality

Unique identification (ID) numbers will be assigned to all trial participants and identifying information will only be accessible to the authorised researchers. Paper copies of assessment tools will all be stored in locked filing cabinets in a secured office. All anonymised data will be stored in an encrypted and password protected excel database. Interviews and focus group discussions will be digitally recorded with participants' consent to record. The interviews will then be transcribed. Recordings will be stored in a secure location and will be destroyed once the qualitative data is published. The quantitative data from the trial will be stored for 10 years in accordance to the Pakistan Institute of Living and Learning Data protection and Storage Policy.

### Adverse event reporting

All the adverse events, whether pertaining to the study or not, will be recorded in detail. In case of a serious adverse event, the PI will immediately notify the collaborating investigators and the ethics committee. Patient safety will be ensured by taking all the appropriate measures.

### Sample size

To have an effect size of 0.45, assuming 5% significance level, 80% power and 10% drop out (Husain *et al*., 2017b) during the study, we need to recruit 300 parents. The objective for which the larger sample size is needed relates to the intra-cluster correlation coefficient (ICC), which measures the degree of similarity in outcome amongst parents in the same cluster; for this, the key is the number of clusters (Rutterford *et al*., 2015). Moreover, groups (and hence clusters) of size around 10 is the optimal size for interventions such as LTP Plus TF-CBT (Biggs *et al*., 2020). We propose a minimum of 15 clusters in each of the LTP + TF-CBT and routine care arms, in order to be able to obtain a relatively precise estimate of the ICC and to check whether it might be greater in the LTP + TF-CBT and routine care arms as the former may have additional variation due to the delivery of the group-based therapy. We, therefore, expect to recruit around 300 parents (approximately 10 each from 15 LTP + TF-CBT and 15 TAU clusters) which will enable the estimation of recruitment and retention rates with sufficiently good precision to inform a full effectiveness trial.

## Assessment measures

### Assessment of feasibility and acceptability

The feasibility of the intervention will be assessed by;
ascertaining whether the intervention is delivered, received and enacted as intendedsession completion rate monitored through session logsthrough qualitative feedback described below

Acceptability of the intervention will be assessed by;
percentage dropouts due to non-acceptabilityrate of serious adverse eventsthrough qualitative feedback described below

**Demographic scale:** A study-specific demographic scale will be used to collect demographic information such as age, education, employment status, socio-economic status etc.

#### Primary outcome

The Clinician-Administered PTSD Scale-5 (CAPS-5) is a 30 item scale and will be used as a primary outcome measure as this is the gold standard structured interview for assessing PTSD, diagnostic status and symptom severity (Weathers *et al*., 2013). Questions target the onset and duration of symptoms, subjective distress, and impact of symptoms on social and occupational functioning. Research evidence with diverse cultures supports that CAPS is reliable and yields consistent scores across items (Weathers *et al*., 2001).

#### Secondary outcomes

Patient Health Questionnaire (PHQ-9) (Kroenke *et al*., 2001) to assess depression. The scale has been translated into Urdu and validated in Pakistan (Ahmad *et al*., 2018). The Urdu version has been used in previous trials in Pakistan (Husain *et al*., 2017b, 2020). The Cronbach's alpha for the PHQ-9 was reported to be 0.91 and the split-half reliability was 0.77 (Ahmad *et al*., 2018).

Generalised Anxiety Disorder Scale (GAD-7) (Spitzer *et al*., 2006) to assess anxiety. The scale has been translated into Urdu and validated in Pakistan (Ahmad *et al*., 2017). The Urdu version has been used in previous trials in Pakistan (Husain *et al*., 2017b, 2020). The Cronbach's alpha for the GAD-7 was reported to be 0.92 and split-half reliability was 0.82 (Ahmad *et al*., 2017).

Client Service Receipt Inventory (CSRI) (Beecham and Knapp, 2001) will be used to collect information about the use of other health services (including the informal sector faith healers/Imams). The CSRI has been used in a previous trial in Pakistan (Husain *et al*., 2014a).

Ages and Stages Questionnaire (ASQ-3) (Squires *et al*., 2009) to assess physical, social, emotional and cognitive development of children.

### Theory of Change (ToC)

The study team uses the Theory of Change approach as a standard framework for bringing about change. The community engagement process will be underpinned by the ToC (Mayne, 2020) causal model of planning, monitoring, evaluation and impact assessment to ensure that the marginalised voices are included in developing the vision. Barriers and challenges are identified through the lens of the end beneficiaries and short, medium and long term outcomes are developed and delivered so real change happens from the perspective of the target group. The ToC is closely embedded in community-based participatory research to engage the community for equity and to ensure that the process of Freirian collective reflection is in place. This reflection process aims to acknowledge the role of community knowledge and fit that can potentially impact the empowerment processes and consequently the power relations and greater equity outcomes within and outside partnerships (Wallerstein *et al*., 2020). The proposed composition of the stakeholder group for this project is truly reflective of the participatory approach by engaging parents with mental health difficulties, CHWs, health professionals, members of non-profit organisations and researchers. The study's ‘Patient and Public Involvement and Engagement (PPIE)’ group will be part of the stakeholder group. People with mental health difficulties make a vulnerable, stigmatised and marginalised group of population in our society (Vigo, 2016). This is particularly true for female survivors of mental health problems in Pakistan (Niaz, 2004). The involvement of the PPIE group in the ToC process throughout the project will ensure that the marginalised voices to be heard.

In practical terms at the planning stage, a workshop with stakeholders including persons with lived experience (the end beneficiaries) as the key stakeholder will come together to explore various elements of the ToC process by developing a shared vision and defining goals in the short, medium and longer term. This stakeholder engagement exercise will help to clarify roles and responsibilities as to who does what and how to achieve the vision. Assumptions will be articulated in the current context. Through our ToC process, stakeholders will identify the social and cultural factors and when the context changes, we will hold further stakeholder workshops to test our assumptions together in order to adapt and refine our model accordingly and with the ownership of all stakeholders. The theory of change will also enable us to show that trial results have been adopted in practice. What barriers and challenges were faced during the trial? What assumptions were made in defining the goal statements? The ToC approach will help mitigate some of the risks around stigma and refusal to participate as a representative group is involved at the inception of the trial. Our ToC pathway will give a detailed and direct understanding of the links between activities that lead to the desired goals. This understanding will lead to better evaluation and measure of progress and in the long term an understanding of impact both planned and unplanned.

### Statistical analysis plan

The study will be carried out in accordance with the CONSORT guidelines. All analyses will be based on the intention-to-treat sample and missing data will be imputed with multiple imputation procedures as implemented in Statistical Package for Social Sciences (SPSS) software (version 27). To assess the primary and secondary outcomes, a two-sided significance level of 0.05 will be employed to enable the detection of a difference between interventions in both directions. Demographics and baseline variables in the two study arms will be compared using various descriptive statistics of means, standard deviations, and proportions. For primary outcome analysis, a two-sample two-sided test of proportions will be used to compare the difference in the rate of PTSD (assessed using the CAPS-5) at 4-month post-randomisation between LTP Plus and TF-CBT and TAU groups. For the secondary analyses, we will compare the proportions similarly for binary outcomes and use tests for comparing means for the continuous outcome. Additionally, we shall use multivariable techniques in assessing the effect of various covariates including baseline measures on outcomes. If required appropriate transformation of continuous variables will be considered. ICC will be calculated to help future cluster-based research on this topic.

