### Randomisation

Randomisation will be computer-generated by an off-site statistician. The unit of a cluster will be Union Councils. A union council forms the second-tier of local government and fifth administrative division in Pakistan, The Union Councils will be randomly allocated to one of the two arms; arm-1 is the intervention group receiving LTP Plus and TF-CBT whereas Arm-2 is routine care.

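### The imputation rule covers all analyses, the ICC included, but makes no provision for Union Council, so the ICC from imputed data would be biased in a direction the plan leaves open

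*Protocol article*

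**What the plan says.** All of the following is in the protocol article.

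- **Randomisation:** "The unit of a cluster will be Union Councils".
- **Statistical analysis plan, scope:** "All analyses will be based on the intention-to-treat sample". The same sentence continues: "missing data will be imputed with multiple imputation procedures as implemented in Statistical Package for Social Sciences (SPSS) software (version 27". No imputation model, predictor list or role for Union Council is given.
- **Statistical analysis plan, output:** the section ends with "ICC will be calculated to help future cluster-based research on this topic". The estimator is not named, and no exception from the imputation rule is made for it.
- **Sample size, purpose:** "The objective for which the larger sample size is needed relates to the intra-cluster correlation coefficient (ICC"). It continues: "We propose a minimum of 15 clusters in each of the LTP + TF-CBT and routine care arms", and the reason given is "in order to be able to obtain a relatively precise estimate of the ICC". It also wants to see whether the ICC differs between the arms, because group delivery may add variation in one of them.
- **Sample size, layout:** "approximately 10 each from 15 LTP + TF-CBT and 15 TAU clusters", with 10% dropout.

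**The concern.** Multiple imputation fills in each missing value from a model. In a cluster trial that model must carry the clusters in the right way, or the completed data will have a different between-cluster variance from the real data. Here the plan names the tool and version, applies it to everything, and lists among its outputs the one quantity that depends directly on between-cluster variance.

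The ICC passes into the design of the full trial through the design effect, 1 + (m - 1) x ICC, where m is the cluster size. An ICC that is too low leaves that trial short of participants; one that is too high makes it larger than necessary. The ICC is also to be compared between arms. A bias that grows with the amount of missing data can produce or hide a difference there when dropout is unequal.

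**Working it through.** **Inputs from the protocol article:** 15 clusters per arm, 30 in all; about 10 parents per cluster (2 x 15 x 10 = 300, the stated total); dropout d = 0.10; imputation applied to all analyses.

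**Assumptions:** the plan gives no ICC value, so there is no ICC figure of its own to reproduce. True ICCs of 0.05 and 0.10 are used. Values are missing completely at random. A 20% missing rate is included only to show how the bias grows.

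**Step 1. Union Council omitted from the imputation model.** Two parents in one cluster keep their covariance only if both were observed, which has probability (1 - d)^2. The total variance is about unchanged. So the ICC from imputed data is about ICC x (1 - d)^2:

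- d = 0.10: factor 0.90^2 = 0.81; 0.05 becomes 0.0405 and 0.10 becomes 0.081.
- d = 0.20: factor 0.80^2 = 0.64.

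A baseline covariate correlated rho with the outcome, and clustered to the same degree, gives part of this back. The factor becomes (1 - d)^2 + [1 - (1 - d)^2] x rho^2. With rho = 0.5 (assumed) and d = 0.10 it is 0.81 + 0.19 x 0.25 = 0.86.

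**Step 2. Union Council entered as a fixed factor.** Each cluster's mean is then estimated from about nine parents. The chance error in that mean, and the error in its random draw, are shared by all imputed parents of the cluster. Shared error counts as between-cluster variance, so the ICC rises.

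**Step 3. Simulation** (30 clusters of 10, 5 imputations, 1,000 runs, within-arm ANOVA estimator, 10% missing):

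| Imputation model | ICC, complete data | ICC, imputed data | Ratio |
|---|---|---|---|
| Arm only | 0.0491 | 0.0394 | 0.80 |
| Arm only | 0.0997 | 0.0805 | 0.81 |
| Arm + baseline covariate | 0.0487 | 0.0413 | 0.85 |
| Arm + baseline covariate | 0.0960 | 0.0828 | 0.86 |
| Arm only, binary outcome | 0.0492 | 0.0391 | 0.80 |
| Arm only, binary outcome | 0.1006 | 0.0823 | 0.82 |
| Union Council as fixed factor | 0.0487 | 0.0708 | 1.45 |
| Union Council as fixed factor | 0.1008 | 0.1213 | 1.20 |

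At 20% missing the arm-only ratio is about 0.64-0.65. An ICC computed from the observed values alone is about unbiased.

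**Step 4. Compare with sampling error.** The standard deviation of the estimated ICC in these runs is about 0.04 at ICC 0.05 and 0.05 at ICC 0.10. The shifts are 0.01 to 0.02 in either direction.

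**Step 5. Effect on a future trial with m = 10.**

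- ICC 0.05: the true design effect is 1 + 9 x 0.05 = 1.45. With Union Council omitted it reads 1 + 9 x 0.0405 = 1.365 (6% low); with the fixed factor, 1 + 9 x 0.0708 = 1.64 (13% high).
- ICC 0.10: the true design effect is 1.90. With Union Council omitted it reads 1 + 9 x 0.081 = 1.73 (9% low); with the fixed factor, 1 + 9 x 0.1213 = 2.09 (10% high).

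**Step 6. Unequal dropout (illustration).** With Union Council omitted, a common true ICC of 0.05, and 10% missing in one arm and 20% in the other, the arms would show 0.05 x 0.81 = 0.041 and 0.05 x 0.64 = 0.032.

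**Step 7. The planned comparison.** The primary analysis is an ordinary two-sample test of proportions, without a cluster term. Its true type I error is about 2 x [1 - Phi(1.96 / sqrt(DE))], with DE the design effect: 10.4% at ICC 0.05 and 15.5% at ICC 0.10. A cluster-adjusted test that used the ICC shrunk by 10% missing data would have 5.7% and 6.2%. Nearly all of the excess comes from the unadjusted test.

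**The case against.** The strongest reply is that the article is condensed and names only the software procedure. How Union Council enters the imputation could be settled in a fuller plan, and nothing in the text says that it is left out. This stands as far as the direction of bias goes. A reader might infer that the imputation is single-level and ignores Union Councils, so that the ICC must be too low. The document does not say so, and a fixed factor would push the ICC the other way.

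It does not remove the point. The section fixes the tool, applies it to all analyses and lists the ICC in the same paragraph. The two ordinary ways of carrying that out, leaving the cluster out or adding it as a categorical predictor, both bias the ICC.

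The second reply is size: at 10% dropout the shift is well within the sampling error of an ICC from 30 clusters. This also stands, and it limits the weight of the point. But sampling error shows in a confidence interval and this bias does not.

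A reader might also infer that the imputation understates the between-cluster variance in the treatment comparison. The planned test of proportions uses no such variance, so there is no cluster-adjusted standard error for the imputation to shrink.

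**Conclusion.** The point holds in a limited form. The plan's imputation rule covers the ICC by its wording, makes no stated provision for Union Council, and so leaves the stated reason for the larger sample open to a systematic bias. At 10% dropout and assumed true ICCs of 0.05 to 0.10, the ICC would be about 14-20% too low if Union Council is omitted. With a fixed factor it would be about 20-45% too high. For clusters of 10 this moves a future trial's size by about 6-9% down or 10-13% up. These figures rest on data missing completely at random and on the assumed ICCs and covariate correlation.

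Two larger claims are not supported. One is that the pilot exists to deliver the ICC: the Abstract gives its aims as acceptability, feasibility and indications of effectiveness, and the ICC is the reason given for the sample size and number of clusters. The other is that this defect calls for replacing the primary test with a mixed model on CAPS-5 scores. The missing cluster adjustment in that test is a separate and larger fault, and the imputation does not cause it.

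**What to change.** - State that the ICC, overall and by arm, will be estimated from the observed 4-month data and not from the imputed data. Use an ANOVA estimator or a random-intercept model for Union Council, and report a confidence interval.
- If imputation is kept for the outcome comparisons, specify a model with a Union Council random effect, run separately by arm.
- Report missing 4-month data by arm and by Union Council beside the ICC, so that readers can judge how unequal the loss was.

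The cost is a change of wording and some extra programming. The multilevel imputation may need software other than the one named. No further data or participants are needed.

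### Union Councils are randomised, but the primary and secondary tests treat parents as independent, so the 5% significance level is not held

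*Protocol article*

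**What the plan says.** The Randomisation section of the protocol article makes the council the unit: "The unit of a cluster will be Union Councils". The Sample size section plans at least 15 councils per arm with about 10 parents each. It defines the ICC as a measure of how alike outcomes are within a cluster. It wants that ICC estimated with reasonable precision, and notes that group delivery may add variation in the therapy arm.

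The Statistical analysis plan section sets the level for primary and secondary outcomes: "a two-sided significance level of 0.05 will be employed". For the primary outcome, "a two-sample two-sided test of proportions will be used to compare the difference in the rate of PTSD (assessed using the CAPS-5", at four months. For the secondary outcomes, "we will compare the proportions similarly for binary outcomes and use tests for comparing means for the continuous outcome". It then adds that "we shall use multivariable techniques in assessing the effect of various covariates including baseline measures on outcomes". Its one statement about clustering is "ICC will be calculated to help future cluster-based research on this topic".

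The section names no mixed model, generalised estimating equation, cluster-robust variance, design-effect correction or council-level summary.

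**The concern.** A two-sample test of proportions takes its standard error from the number of parents, as if each had been randomised separately. Here the council was randomised, and the therapy is delivered in groups within it. If parents in one council tend to have similar outcomes, the arm difference varies more than that standard error allows. The test then rejects a true null hypothesis more often than 5% of the time. The same applies to unadjusted tests of means for the continuous secondary outcomes.

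The design section prepares for within-council correlation and the analysis section ignores it. At stake is the effectiveness signal. An apparent benefit on PTSD rate could come from differences between councils alone, and that result is meant to inform whether and how a full trial is run.

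**Working it through.** **Inputs**

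- From the article: 15 councils per arm (the stated minimum), about 10 parents each, 10% dropout, two-sided 5% level.
- Parents analysed per council, m: 10 × 0.9 = 9. Because the article plans multiple imputation on the intention-to-treat sample, m = 10 is shown as well.
- Assumed, because the article gives no value: ICC from 0.01 to 0.10, and PTSD rates at four months of 50%, 60% and 70% in the simulations.

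**The plan's own figure.** The Sample size section begins "To have an effect size of 0.45, assuming 5% significance level, 80% power and 10% drop out" and arrives at 300. Reading 0.45 as a standardised mean difference:

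- n per arm = 2 × (1.960 + 0.842)² / 0.45² = 77.5, so 78; total 156.
- With 10% dropout: 156 / 0.9 = 173.3, so 174.

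The stated inputs give 174, not 300. The figure may simply be 30 councils × 10 parents. If the gap is instead an unstated allowance for clustering, then 270 analysed / 156 = 1.73 = 1 + (m − 1) × ICC. That implies an ICC of 0.73/9 = 0.08 at m = 10, or 0.73/8 = 0.09 at m = 9. The finding does not depend on which explanation is right.

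**Formulas**

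- Design effect: DE = 1 + (m − 1) × ICC
- True two-sided error of the nominal 5% test: 2 × [1 − Φ(1.96 / √DE)]
- Shortfall in the width of an unadjusted confidence interval: 1 − 1/√DE

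Example at ICC 0.05 and m = 9: DE = 1 + 8 × 0.05 = 1.40; 1.96/√1.40 = 1.66; error = 9.8%; interval shortfall = 1 − 1/1.183 = 15%.

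| Assumed ICC | DE (m = 9) | True error (m = 9) | Interval too narrow by (m = 9) | True error (m = 10) |
|---|---|---|---|---|
| 0.01 | 1.08 | 5.9% | 4% | 6.1% |
| 0.02 | 1.16 | 6.9% | 7% | 7.1% |
| 0.05 | 1.40 | 9.8% | 15% | 10.4% |
| 0.08 | 1.64 | 12.6% | 22% | 13.5% |
| 0.10 | 1.80 | 14.4% | 25% | 15.5% |

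At ICC 0.09 and m = 9, DE = 1.72 and the error is 13.5%.

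**Simulation check** (beta-binomial outcomes, no treatment effect, 15 councils per arm)

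- PTSD rate 60%, m = 9, 40,000 trials per ICC: the unadjusted test rejected in 7.1%, 10.3%, 14.0% and 14.6% of trials at ICC 0.02, 0.05, 0.09 and 0.10.
- PTSD rate 70%, 100,000 trials: 9.8% (m = 9) and 10.4% (m = 10) at ICC 0.05; 14.8% and 15.6% at ICC 0.10.
- PTSD rate 50%, 100,000 trials: 9.2% and 11.3% at ICC 0.05; 13.7% and 16.5% at ICC 0.10. The wider spread between m = 9 and m = 10 is already present at ICC zero (4.6% and 5.8%), so it is not caused by clustering.
- In the 50% and 70% simulations, a t-test on the 15 + 15 council proportions with 28 degrees of freedom rejected in 4.9% to 5.2% of trials at every ICC from 0 to 0.10.

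**The case against.** The strongest reply is that this is a pilot. Its aims are feasibility, acceptability and signs of effectiveness, its size is also justified by the precision of the ICC and of recruitment and retention rates, and no stated rule ties a full trial to p < 0.05. That stands, and it limits the consequence: the feasibility results and the ICC estimate are untouched. It does not rescue the test, because the article still sets a 5% level, claims 80% power and names a primary outcome test.

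It is also fair that the ICC is not given. The article defines it and plans to estimate it but does not assert that it is positive, and at 0.01 the inflation is small. The size of the error is therefore conditional, although its direction is the same for any positive ICC. The article also names no confidence interval for the treatment effect, so the interval shortfall applies to intervals computed on the same basis as the tests. The main argument rests on the p-values.

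Three further defences fail:

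- A separate analysis plan might handle clustering, but the article names the test, so a correct plan would contradict it.
- The multivariable analyses are additional, concern covariates and do not mention councils.
- The reference to CONSORT names no method of analysis.

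**Conclusion.** The point holds and must be fixed. The prescribed primary test, and the secondary tests as named, do not match the unit of randomisation. With 15 councils per arm and 9 parents analysed in each, the real type I error of the nominal 5% test runs from 5.9% at an assumed ICC of 0.01, through 9.8% at 0.05, to 14.4% at 0.10. If an allowance for clustering explains the target of 300, the implied ICC of 0.08 to 0.09 puts the error at about 13% to 14%. These sizes rest on assumed ICCs, equal council sizes and the same ICC in both arms. The conclusion that the level is exceeded needs only a positive ICC.

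**What to change.** Rewrite the Statistical analysis plan section so that every between-arm comparison respects the Union Council.

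- **Primary outcome.** Compare the council-level PTSD proportions between arms with a t-test (28 degrees of freedom with 15 councils per arm), and report the difference in rates with its 95% confidence interval. This keeps the effect measure the article already uses. The alternative is a logistic mixed model with a council random intercept and a small-sample correction. That gives a conditional odds ratio, so the change of effect measure would have to be stated. Choose one in advance as primary.
- **Secondary outcomes and covariate analyses.** Apply the same rule: council-level means or proportions, or mixed models (linear for scores) with a council random intercept and small-sample correction.
- **Extra variation in the therapy arm.** Since the article expects it may occur, allow the between-council variance to differ by arm, for example with the unequal-variance form of the t-test.
- **Imputation.** Include the council in the imputation model, so that imputed values do not weaken the within-council correlation.
- **ICC.** Keep the planned estimate and report it by arm.

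The cost is a rewritten analysis section and a changed imputation model. No further data are needed, since estimating the ICC already requires council identifiers. Intervals become wider and power falls. For the stated effect size of 0.45 with 135 parents analysed per arm and m = 9, approximate power is 93% at ICC 0.02, 88% at 0.05, 82% at 0.08 and 79% at 0.10, and slightly lower once the 28 degrees of freedom are allowed for. These figures are for a standardised mean difference, so power for a difference in PTSD rates should be stated separately.

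### The primary comparison of PTSD rates makes no use of baseline CAPS-5 severity, and the scale of the 0.45 effect behind its 80% power is not stated

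*Protocol article*

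**What the plan says.** - **Primary test.** The Statistical analysis plan section names a "two-sample two-sided test of proportions will be used to compare the difference in the rate of PTSD (assessed using the CAPS-5" at 4 months after randomisation, LTP Plus TF-CBT against TAU. For both primary and secondary outcomes, "a two-sided significance level of 0.05 will be employed".
- **Instrument.** The Primary outcome section chooses CAPS-5 because "this is the gold standard structured interview for assessing PTSD, diagnostic status and symptom severity". It therefore yields a severity measure as well as a diagnosis.
- **Availability at baseline.** Meeting CAPS-5 criteria is an inclusion criterion. The Procedure section has a trained researcher give the interview to each otherwise eligible parent (the acronym is misspelt there, but the instrument is clear).
- **Use of baseline data.** As an addition to the tests above, "we shall use multivariable techniques in assessing the effect of various covariates including baseline measures on outcomes".
- **Sizing.** The Sample size section reads "To have an effect size of 0.45, assuming 5% significance level, 80% power and 10% drop out", and concludes "we need to recruit 300 parents", as about 10 from each of 15 + 15 clusters. It gives no scale for the 0.45, no PTSD rate for either arm and no ICC value.

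**The concern.** All participants have PTSD at entry, so baseline diagnosis is constant and cannot serve as a covariate. The usable baseline information is CAPS-5 severity, and the primary test does not use it. A parent who enters far above the diagnostic threshold is less likely to have dropped below it by 4 months than one who enters just above. With only about 30 Union Councils randomised, the arms can differ by chance in entry severity, and an unadjusted difference in rates carries that imbalance into the estimate. The same omission leaves explainable outcome variance in the standard error.

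The sizing adds a second difficulty. A test of two proportions is sized from two rates, or from a stated transform of them. The article gives one effect size without a scale, so a reader cannot tell what difference in PTSD rate the 80% power refers to.

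**Working it through.** **Inputs from the article:** effect size 0.45; two-sided 5%; 80% power; 10% dropout; 300 parents; 15 + 15 clusters of about 10. After dropout this is 300 × 0.9 = 270, or 135 per arm and 9 per cluster.

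**Assumptions not in the article:** ICC 0.05; TAU PTSD rate at 4 months 50% to 80%; baseline to follow-up correlation r of 0.2 to 0.5; diagnosis treated as a cut on a normal latent severity.

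**1. The plan's own figure.** With 0.45 as a standardised mean difference, n = 2(1.96 + 0.8416)² / 0.45² = 77.5, so 78 per arm and 156 in total. Dropout gives 156 / 0.9 = 173.3, so 174. The stated 300 does not follow from the stated inputs alone. It needs a design effect of about 270 / 156 = 1.73, i.e. an ICC of about 0.08 (10 per cluster) or 0.09 (9 per cluster), which the article does not give.

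**2. Size of chance imbalance at baseline.** With 150 per arm, 10 per cluster and ICC 0.05, the design effect is 1 + 9 × 0.05 = 1.45. The SD of the arm difference in mean baseline severity is √(2 × 1.45 / 150) = 0.14 SD. At r = 0.2 to 0.5, an imbalance of that size moves the unadjusted follow-up difference by about 0.03 to 0.07 SD.

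**3. Gain for the severity score.** Design effect 1 + 8 × 0.05 = 1.4; effective n = 135 / 1.4 = 96.4 per arm. Noncentrality = 0.45 / √(2(1 − r²) / 96.4), with a noncentral t on 28 df.

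| r | noncentrality | power |
|---|---|---|
| 0 (unadjusted) | 3.12 | 85% |
| 0.2 | 3.19 | 87% |
| 0.4 | 3.41 | 91% |
| 0.5 | 3.61 | 94% |

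**4. Gain for the PTSD rate.** Under the latent model, the share of binary variance explained by baseline severity is [Φ₂(c, c; r²) − p²] / [p(1 − p)], where c = Φ⁻¹(p) and Φ₂ is the bivariate normal distribution function with correlation r². Pooled over the two arms for TAU rates of 50% to 80%, this is about 5% to 6% at r = 0.3 and 15% to 16% at r = 0.5. A 16% reduction multiplies the test statistic by 1/√0.84 = 1.09. For the score at r = 0.5 the factor is 1/√0.75 = 1.15.

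**5. What 0.45 means for the planned test, before clustering and dropout.**

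*Read as SD units:* p₁ = Φ(Φ⁻¹(p₀) − 0.45), and n = (1.96 + 0.8416)²[p₀(1 − p₀) + p₁(1 − p₁)] / (p₀ − p₁)².

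| TAU rate p₀ | p₁ | n per arm, yes/no | n per arm, score |
|---|---|---|---|
| 50% | 32.6% | 122 | 78 |
| 60% | 42.2% | 120 | 78 |
| 70% | 53.0% | 124 | 78 |
| 80% | 65.2% | 139 | 78 |

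*Read as Cohen's h:* the test of proportions needs about 78 to 81 per arm for TAU rates of 50% to 90%, so it keeps its nominal power. In the set-up of step 3 that power is about 85% to 87%. The underlying shift is then larger, about 0.57 to 0.67 SD.

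**The case against.** - **Remission is a legitimate endpoint.** Everyone enters with the diagnosis, so no longer meeting criteria is recognisable and clinically meaningful. This stands. Replacing it by the score would change the estimand, which is a trade-off for the sponsor and not the correction of an error.
- **Baseline is not ignored.** The multivariable sentence does mention baseline measures, and model details may sit in an analysis plan that is not shown. This stands for the plan as a whole. It does not reach the primary comparison, which the article itself fixes as an unadjusted test; the sentence is additional and concerns covariate effects on outcomes.
- **Much of the power is thrown away.** A reader might infer this from step 5. The documents do not support it as a general statement, because 0.45 has no stated scale and under Cohen's h the planned test keeps its nominal power. Even in SD units the contrast is easily overstated. With ICC 0.05 for both scales, the yes/no test has 61% to 68% power against 85% for the score. The latent model, however, implies an ICC of only about 0.03 for the diagnosis, which gives about 67% to 73%.
- **Secondary scores are compared as raw follow-up means.** A reader might infer this too. The article says only that means will be compared and does not say whether these are follow-up values or changes.
- **Entry criteria restrict the baseline range.** This stands. Restriction tends to lower the baseline correlation, and at r = 0.2 the gain is about two percentage points.
- **It is a pilot.** This stands in part. Feasibility and ICC estimation are central, so lost power matters less than in a confirmatory trial. The article nevertheless claims 80% power and fixes a 5% primary test.

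**Conclusion.** The point holds as one about adjustment and about stating the basis of the power. The primary comparison leaves out a prognostic measure that the trial collects on everyone, and with about 30 clusters this costs precision and exposes the estimate to chance imbalance. The gain from adjusting ranges from small to moderate: for the score, 2 to 9 percentage points of power at correlations of 0.2 to 0.5; for the rate, about 5% to 16% of the variance at latent correlations of 0.3 to 0.5. These figures depend on the assumed ICC, TAU rate, correlation and latent-normal model. Separately, the 80% power cannot be tied to the planned test until the scale of 0.45 and the expected PTSD rates are given. The documents do not show that choosing the diagnosis as primary endpoint is wrong.

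**What to change.** 1. Keep the PTSD rate at 4 months as primary if the sponsor prefers. Estimate the arm difference in a model that treats Union Council as the cluster and adjusts for city and baseline CAPS-5 severity, and report the marginal risk difference with its confidence interval.
2. Prespecify the 4-month CAPS-5 severity score as a key secondary analysis, in a linear mixed model with arm, baseline CAPS-5 score, city and a random intercept for Union Council.
3. Adjust PHQ-9, GAD-7 and ASQ-3 for their own baseline values.
4. State in the Sample size section whether 0.45 is a standardised mean difference or Cohen's h, and give the PTSD rates in each arm to which the 80% power applies.

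The cost is wording in the analysis and sample size sections. No visit or instrument is added, but the severity score from the entry CAPS-5 interview must be kept and not only the diagnosis. A model-based risk difference needs slightly more explanation than a raw one; the crude rates can be shown beside it.
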